| **Purpose** | ○ **Primary purpose:**  - Analysis of the effect of using a smartphone app-based human coaching program on the patient's symptoms and quality of life in patients who underwent gastrectomy for stage 1 gastric cancer  - Comparison of food restriction scale scores of EORTC QLQ STO22 at 3 months after surgery in patients who used smartphone app and patients who received nutrition counseling  ○ **Secondary purpose:**  - Comparison of food restriction scale scores of EORTC QLQ C30 and STO22 at 6 months after surgery  - Comparison of food restriction scale scores of EORTC QLQ C30 and STO22 at 12 months after surgery  - Meal volume, biomarkers (BMI, muscle mass, etc.), blood test results | | | | |
| **Background** | - Patients who underwent gastrectomy suffer from symptoms such as abdominal pain, diarrhea, nausea/vomiting, increased pulse, weakness, and hypoglycemia (gastric resection syndrome) after a meal due to the resection of the pylorus that controls the speed of food movement between the stomach and small intestine. Symptoms are especially severe when the patient rushes to eat food, eats a large amount at once, and eats high-sugar foods.  - During the hospitalization period, the patient begins with Mieum and proceeds with a small amount of porridge, but after discharge, he suffers trial and error because he does not know how to proceed in his daily life. In addition, after being diagnosed as a cancer patient, people around them listen to unverified stories and eat mainly with certain foods, or they may not be able to consume enough nutrition due to restrictions on certain foods. Sometimes suffered.  - Currently, a smartphone app (Noom) that provides a 1:1 personalized coaching service is being used among the general public to keep a daily meal diary and calculate meal calories for weight loss. Noom not only makes it easy for users to enter the food eaten during the day based on the food database, but also helps the coach in charge check daily to keep the dietary control.  - If a gastric cancer patient uses Noom in the process of nutritional adaptation after surgery, coaching can be performed at an appropriate time according to the patient's situation. As a result, patients and their caregivers are expected to reduce trial and error related to dietary adaptation and reduce gastrectomy syndrome. | | | | |

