| **Study method** | - Patients who are scheduled to undergo gastrectomy for stage 1 gastric cancer are randomly assigned either to the mHealth group or the face-to-face counseling group. Patients in the mHealth group (N=90) will use mobile application for 3 months after discharge and those who in the face-to-face counseling group (N=90) will receive general nutrition counseling at 1 month and 3 months after gastrectomy.  - QOL, body component, and nutritional outcomes will be compared between the two groups.  - When obtaining the consent form, the mHealth group will be provided with a simple noom instruction manual and a noom meal record guide, and will be informed of how to use it.  - In addition, individual coaching will be given through articles and messengers on how to manage post-gastrectomy such as weight, diet, and exercise on the mobile app for 3 months from the discharge date.  - Survey response on quality of life at outpatient visits 1, 3, 6, 12 months after surgery  [figure not shown]  * The allowable date of visit at 1, 3, 6, and 12 months after surgery is 1 month before and after. | | | | |
| **Intervention method** | **- mHealth group:** After being discharged from hospital, patients will receive coaching using a smartphone app for 3 months. When the patient is discharged from the hospital, he downloads the Noom app on his or her mobile phone, registers, and then uses the Noom program. In addition, a personal coach is assigned to provide appropriate coaching to the patient on the app.  **-Face-to-Face group:**　Patients will receive individual nutrition counseling from a clinical nutritionist at the hospital at 1 month and 3 months after surgery. | | | | |
| **Evaluation** | Between the mHealth and face-to-face groups  - Comparison of scores of EORTC QLQ-C30 and STO22 at 1, 3, 6, and 12 months postoperatively.  - Comparison of meal amount at 1, 3, 6, and 12 months postoperatively.  - Comparison of body component (BMI, muscle mass, etc) at 1, 3, 6, and 12 months postoperatively.  - Comparison of nutritional outcomes (hemoglobin, albumin, protein, cholesterol) at 1, 3, 6, and 12 months postoperatively | | | | |

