**(2) Dietary adaptation of the patient**

- Patients receive nutritional counseling during the hospitalization period, but when they return to their daily life after discharge, there is no separate education on how to eat and how to adjust, resulting in various trials and errors.

- In particular, after being diagnosed as a cancer patient, there are cases where people around us hear unverified stories and eat mainly with certain foods, or they may not be able to consume enough nutrition due to restrictions on certain foods.

- They are also not well aware of postgastrectomy syndrome, so they constantly experience discomfort after eating.

- This postgastrectomy syndrome is most severe in the early postoperative period and gradually relieves after dietary adaptation.

(3) **Diet management using a smartphone app**

[figure not shown]
- Currently, for weight loss, a smartphone app (Noom) is being used that keeps a daily meal diary, calculates meal calories, and provides 1:1 customized coaching service.

- Noom not only makes it easy for users to enter the food eaten during the day based on the food database, but also helps the coach in charge check daily to keep the dietary control.

- If Noom is used in the process of dietary adaptation after surgery for gastric cancer patients, it is expected that balanced nutritional intake will be achieved through appropriate dietary disorders. In addition, by providing information on gastrectomy syndrome, it is possible to reduce and prevent gastrectomy syndrome.

- Also, as Noom actively encourages exercise therapy, the patient is motivated for proper exercise.

- This is expected to reduce the patient's symptoms and improve the quality of life.

(4) **Previous literature review**

- In the past literature, the results that weight control and metabolic syndrome control were significantly improved when using a smartphone app were published in several papers.

- There have also been studies showing that breast cancer survivors, which are highly related to obesity, lose weight, increase vegetable intake, and increase exercise volume when nutritional control using a smartphone app is used.

- Regarding stomach cancer, a study on improving lung capacity with a mobile self-monitoring tool has been published, and studies related to nutrition or diet have only been introduced with protocols so far.

[figure not shown]

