**- Results**

1) Eating restriction score of EORTC QLQ-STO22

-Preoperative, median value: 6.7 (IQR 6.7, 13.3)

-Postoperative 1-month, median value: 30.0 (IQR 13.3, 56.7)

-Postoperative 3-month, median value: 20.0 (IQR 3.3, 26.7)

2) Satisfaction (n=13)

: The use of the app helped adapt to the diet and the overall satisfaction was very high.

-Ease of use of the app – Strongly yes (9), yes (3), no (1)

-Ease of understanding of the information provided - Strongly yes (8), yes (4)

-Usability of using the app - Strongly yes (12), yes (1)

-Appropriateness of time spent in app - Strongly yes (8), yes (5)

-Overall satisfaction: Strongly yes (11), yes (2)

(6) **Benefit**

- Evaluation of whether dietary management using a smartphone app contributes to improving the patient's quality of life in patients undergoing gastrectomy

- Development of coaching materials for patients undergoing gastrectomy

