**(5) Outcome parameters**

- Comparison of food restriction scale score of EORTC QLQ C30, STO22:

Whether there is a significant difference in the mean value is evaluated by the p-value of the t-test. Since the 1st month questionnaire is the primary endpoint, it is evaluated individually and the significance of the mixed model's p-value is evaluated to see if there are overall differences in the values ​​measured several times.

- Inbody values ​​such as meal volume, BMI, muscle mass, and blood tests were compared with the average value at 3 months, and the significance was evaluated by the p-value of the mixed model to see if there was a difference overall.

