**8. Study method**

**(1) Study method**

- Patients who are scheduled to undergo gastrectomy for stage 1 gastric cancer are randomly assigned either to the mHealth group or the face-to-face counseling group. Patients in the mHealth group (N=90) will use mobile application for 3 months after discharge and those who in the face-to-face counseling group (N=90) will receive general nutrition counseling at 1 month and 3 months after gastrectomy.

[figure not shown]

- Patients will receives nutritional counseling at 1 month (30 days) and 3 months (90 days) after gastrectomy by randomization. The allowable date of visit to the hospital is 1 month before and after 1, 3, 6, 12 months after surgery. If the patient does not visit the hospital and cannot be contacted, the study coordinator attempts to contact the hospital by phone or text once a week for a month. Subject will be eliminated from the study if he did not visit the hospital at all the follow-up period.

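### The visit window of 1 month either side lets the 1-month primary questionnaire be taken as late as day 60, where the 3-month window begins, and timing on that scale can shift a patient's score by about the planned 5-point difference

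*Protocol*

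**What the plan says.** Section 8(1) of the protocol states: "The allowable date of visit to the hospital is 1 month before and after 1, 3, 6, 12 months after surgery". The synopsis row on study method repeats it: "The allowable date of visit at 1, 3, 6, and 12 months after surgery is 1 month before and after". Section 8(1) also fixes the nominal days by scheduling "nutritional counseling at 1 month (30 days) and 3 months (90 days) after gastrectomy".

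The quality-of-life questionnaires are answered at these outpatient visits (synopsis, study method; schedule table in the study diagram). No narrower window is set for them.

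Section 7(5) says: "Since the 1st month questionnaire is the primary endpoint, it is evaluated individually". The test is also stated there: "Whether there is a significant difference in the mean value is evaluated by the p-value of the t-test". Section 2(1) and the sample-size paragraph in section 6(2) likewise use 1 month. The synopsis purpose row names a different time point: "Comparison of food restriction scale scores of EORTC QLQ STO22 at 3 months after surgery".

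The app is installed at discharge and used for 3 months from then (synopsis, intervention method). Section 4(4) drops patients whose stay exceeds 3 weeks because of complications, so stays of up to 3 weeks remain in the trial. The face-to-face arm receives its counselling in hospital at 1 and 3 months; the app arm is coached remotely.

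On the course of symptoms, section 1(2) says: "This postgastrectomy syndrome is most severe in the early postoperative period and gradually relieves after dietary adaptation".

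**The concern.** A tolerance of 1 month is modest for a 6- or 12-month visit. For a 1-month visit it is as long as the follow-up time itself. Three things follow.

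- **What is measured is loosely defined.** Scores taken weeks apart, at different stages of recovery, are all labelled 1 month and enter the same t-test.
- **Exposure varies.** The amount of coaching received by the time of the primary score depends on both discharge date and visit date.
- **Visits are not separable at the boundary.** The 1-month and 3-month windows share day 60.

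At stake is mainly bias. If the two arms complete the form at different average times, the difference in recovery stage is read as a treatment effect. The patients know their arm, and the reasons to attend are not identical: only the face-to-face arm has counselling in hospital at these visits. The protocol does not say whether the form is completed before or after that counselling.

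**Working it through.** **Inputs.** Nominal days 30 and 90, window 30 days either side (section 8(1)). Expected scores 30 (app) and 35 (control), SD 10, alpha 0.05, power 80%, 65 per group (section 6(2)). Pilot medians of the eating restriction score: 6.7 before surgery, 30.0 at 1 month, 20.0 at 3 months (section 1(5)). Sidedness is not stated; two-sided is assumed.

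**1. The plan's own figure.** n per group = 2 × (1.960 + 0.842)² × 10² / 5² = 62.8, so 63; the exact t-test gives 64. The stated 65 is reproduced to within 2 patients. The one-sided figure, 50, does not fit. With 65 per group the standard error of the difference is 10 × √(2/65) = 1.754, and power for 5 points is 81%.

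**2. Windows.** 1 month: 30 ± 30 = day 0 to 60. 3 months: 90 ± 30 = day 60 to 120. They meet at day 60. Day 0 is only an arithmetic bound, because the form is completed at an outpatient visit and so after discharge.

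**3. Coaching exposure.** A patient discharged on day 21 and seen on day 25 has had 25 − 21 = 4 days of app use. The same patient seen on day 60 has had 39. Both count as 1 month. App use ends 3 months after discharge, at day 90 plus the length of stay, so at about day 111 for a 21-day stay and earlier for shorter stays. The day 60 to 120 window therefore mixes scores during and after app use.

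**4. Slope.** (30 − 20) / 60 days = 0.167 points per day, or 5.0 per month. The interpolated score is 30 at day 30, 27.5 at day 45 and 25 at day 60. A form at day 60 instead of day 30 is 5 points lower, equal to 35 − 30.

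**5. Bias if mean visit day differs between arms.** Bias = days × 0.167. Type I error is two-sided under no true effect. Power is for a true 5-point effect with the bias working against it.

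| Difference in mean day | Bias (points) | Share of 5 points | Type I error | Power |
|---|---|---|---|---|
| 0 | 0 | 0% | 5% | 81% |
| 3 | 0.5 | 10% | 5.9% | 73% |
| 7 | 1.2 | 23% | 10% | 59% |
| 14 | 2.3 | 47% | 26% | 33% |

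The slope is uncertain. At 2.5 to 7.5 points per month (an assumed range), the bias is 0.6 to 1.75 points for 7 days and 1.2 to 3.5 for 14 days.

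**6. Equal timing in both arms.** Visits spread evenly over days 30 to 60 cover 5 points, adding an SD of 5/√12 = 1.44. Total SD is √(100 + 2.08) = 10.1 and power is 80.5%, against 81.3% without the spread.

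**7. If 3 months is primary.** The same slope gives about 5 points over days 60 to 90, so the early half of that window has the same problem.

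**The case against.** The strongest case on the other side is that harm is conditional. Both arms are due at the same outpatient visits for the same assessments, and no passage says they will attend on different days. Without a timing difference there is no bias, and step 6 shows that the added noise hardly matters. This stands, and it limits the point to a possible bias of unknown size.

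The slope is also weak evidence. It joins two medians from a single-arm pilot of app users (20 enrolled, 6 dropped out), so it mixes recovery with any app effect. This stands too.

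The error rates rest on the planned SD of 10. The pilot's 1-month interquartile range (13.3 to 56.7) suggests (56.7 − 13.3)/1.349 = 32 if scores were roughly normal. At that SD the 7- and 14-day biases would raise type I error only to about 5.5% and 7%. The bias in points would not change.

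Several stronger readings are tempting but are not supported:

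- *A 1-month form could precede app start.* Forms are completed at outpatient visits and the app is installed at discharge, so a form can barely follow the scheduled start but not precede it.
- *Symptoms change fastest in this period.* Section 1(2) says they are most severe early and then ease; it says nothing about rate. The pilot has no value between the preoperative score and 1 month, so the shape over days 0 to 30 is unknown.
- *Timing could create a spurious treatment effect of the full 5 points.* Five points is the shift for one patient. A group difference that large needs mean visit days 30 days apart, which is not realistic.
- *The spread of visits costs substantial power.* Extending the later slope back to day 0 gives an SD of 10/√12 = 2.9, but that extrapolates where there are no data. Even then total SD is 10.4 and power about 78%.

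Finally, rules for assigning out-of-window forms and sensitivity analyses are ordinary SAP content, and the SAP is not at hand. Their absence from the protocol is not the criticism; the stated window is.

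**Conclusion.** The point holds as a design weakness worth correcting, not as a demonstrated bias. The protocol fixes a rule that lets the primary score be taken at any time from soon after discharge to day 60, leaves a day-60 form attributable to either of two visits, and lets coaching exposure at 1 month range from a few days to well over a month. These statements follow from the text and do not depend on the pilot.

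The size does depend on it: about 5 points for one patient seen at day 60 instead of day 30, and about 1.2 or 2.3 points of bias if the arms' mean visit days differ by 7 or 14. This assumes linear change between the pilot medians and, for the error rates, SD 10 and 65 evaluable per group. A difference in timing is possible because only one arm has in-hospital counselling at these visits, but it is not shown. The conclusion is the same whichever of the protocol's two stated primary time points is confirmed.

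**What to change.** Keep the present window for clinic attendance and leave the counselling schedule alone. For the questionnaire:

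- **Set a narrower window**, for example 1 month ± 7 days (day 23 to 37) and 3 months ± 14 days (day 76 to 104). These widths are illustrations. They do not overlap, so a day-60 form is no longer ambiguous. On the pilot slope the largest late shift at 1 month falls from 5.0 to 1.2 points.
- **Offer phone or paper completion**, identically in both arms, when the clinic visit falls outside the window. Do not use the app for this: only one arm has it, so the mode of completion would differ by arm. Coordinators already phone or text patients who miss visits, but collecting forms that way would be a new task.
- **Record the completion date** of every form.
- **Add a sensitivity analysis** of the primary score using actual days since surgery, in the protocol or the SAP.

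The cost is a short amendment and some coordinator time. Some forms will be completed remotely, and a few will fall outside the window. If visits have already begun, recording dates and the sensitivity analysis are still worth doing.

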**(4) Drop-out criteria**

1. Patients who have not undergone distal gastrectomy or total gastrectomy

1. The pathology test result is stage II or higher after gastrectomy
2. Patients who need adjuvant chemotherapy after gastrectomy

4. The hospital stay exceeds 3 weeks due to complications

5. Patients request withdrawal of participation

6. Patients having difficulty in collecting data suitable for the purpose of the study because they have not visited at all 1, 3, 6, and 12 months

1. **Study diagram**

|  | Informed consent | |  |
| --- | --- | --- | --- |
|  |  |  |  |
|  | Screening | |  |
|  |  |  |  |
|  | Gastrectomy | |  |
|  |  |  |  |
|  | Follow-up at 1, 3, 6, 12 months after operation | |  |

| **Data** | **Preop** | **Op** | **POD5** | **POD1m** | **POD3m** | **POD6m** | **POD12m** |
| --- | --- | --- | --- | --- | --- | --- | --- |
| age, sex, height, past medical history, smoking, alcohol, concomitant medications | O |  |  |  |  |  |  |
| operating day, operation method |  | O |  |  |  |  |  |
| pathological results of gastric cancer, postoperative complications |  |  |  | O |  |  |  |
| body weight | O |  | O | O | O | O | O |
| body component such as muscle mass measured with a body composition analyzer | O |  |  | O | O | O | O |
| EORTC QLQ C30, STO22 | O* |  |  | O | O | O | O |
| Hb, Protein, Albumin, Cholesterol | O |  | O |  | O | O | O |

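### The self-reported primary score has no stated route other than a clinic visit, and at months 1 and 3 only the control programme is delivered at that visit; a remote route and a clearer attendance rule are cheap improvements

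*Protocol*

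**What the plan says.** **Collection.** The synopsis (Study method) has "Survey response on quality of life at outpatient visits 1, 3, 6, 12 months after surgery". The table under the study diagram places QLQ-C30 and STO22 before surgery and at the same four visits. No section gives another way to complete them.

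**Delivery of the two programmes.** For the control arm, the synopsis (Intervention method) says "Patients will receive individual nutrition counseling from a clinical nutritionist at the hospital at 1 month and 3 months after surgery". For the app arm it says "After being discharged from hospital, patients will receive coaching using a smartphone app for 3 months". Section 8(1) agrees with both.

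**Primary time point.** The synopsis (Purpose) names "Comparison of food restriction scale scores of EORTC QLQ STO22 at 3 months after surgery". Section 7(5) says "Since the 1st month questionnaire is the primary endpoint, it is evaluated individually", and section 2(1) also gives 1 month. The protocol therefore has two candidate primary visits.

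**Non-attenders.** Section 8(1) has the coordinator try to reach them "by phone or text once a week for a month", without saying what the contact is for or when it starts relative to the visit window of one month either side. It then states: "Subject will be eliminated from the study if he did not visit the hospital at all the follow-up period". Drop-out criterion 6 (synopsis and section 4(4)) covers patients whose data are hard to collect "because they have not visited at all 1, 3, 6, and 12 months".

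**Shared assessments.** The same table schedules body composition for both arms at 1, 3, 6 and 12 months, blood tests at 3, 6 and 12 months, and pathology and complications at 1 month.

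**The concern.** A questionnaire the patient fills in does not need a hospital visit, but here a missed visit means a missing score. At both candidate primary visits the control patient comes for the allocated programme as well as the assessments. The app patient has the programme at home and comes for the assessments alone. Eating difficulty after gastrectomy may also affect whether a patient attends. If attendance depends on both arm and recovery, the t-test at the primary visit compares selected patients, and the 30% drop-out allowance does not help: it restores numbers, not comparability.

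The elimination rule is a separate and smaller problem. It removes randomised patients on the basis of attendance after randomisation, and criterion 6 is worded so that it can be applied in two quite different ways.

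**Working it through.** **1. The plan's own figures.** Inputs from section 6(2): means 30 and 35, SD 10, alpha 0.05 (two-sided assumed, as sidedness is not stated), power 80%.

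n per group = 2 × (1.960 + 0.842)² × 10² / 5² = 62.8, so 63; the t-based calculation gives 64. The stated 65 is consistent with this. Inflation for 30% drop-out: 63 / 0.70 = 90 per group, as stated. (From 65 it would be 65 / 0.70 = 92.9, so 93; a side remark that does not bear on this point.)

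**2. Shift caused by missing scores.** Let m be the share missing in an arm and d the mean of missing patients minus the mean of observed patients. Higher scores are worse, as the pilot's rise from 6.7 before surgery to 30.0 at 1 month implies. The observed mean equals the true mean minus m × d. So

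shift in (app − control) = −(m_app × d_app) + (m_ctrl × d_ctrl).

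The protocol gives neither m by arm nor d, so every row below is an assumption. A negative shift favours the app.

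| Missing, app vs control | d (points worse, both arms) | Shift (points) | Share of the planned 5 points |
|---|---|---|---|
| 10% vs 10% | any | 0 | 0% |
| 10% vs 5% | 5 | −0.05 × 5 = −0.25 | 5% |
| 10% vs 5% | 10 | −0.05 × 10 = −0.50 | 10% |
| 10% vs 5% | 20 | −0.05 × 20 = −1.00 | 20% |
| 15% vs 5% | 5 to 10 | −0.5 to −1.0 | 10% to 20% |
| 30% vs 10% | 5 to 10 | −1.0 to −2.0 | 20% to 40% |

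For scale, the standard error of the difference with 65 per arm is 10 × √(2/65) = 1.75 points. With SD 10 and 90 randomised per arm, the 15% vs 5% row moves the two-sided type I error from 5% to between 6% and 10%, and the 30% vs 10% row to between 9% and 22%.

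If the direction differs by arm (missing app patients worse, missing control patients better, by 5 to 10 points), equal 10% missingness also gives a shift: −(0.10 × d) − (0.10 × d) = −1.0 to −2.0 points.

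**3. The two readings of criterion 6.** Assume, for illustration only, that each visit is missed independently with probability 10%.

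- Removed if no visit is attended: 0.1⁴ = 0.01% of patients. None of them has a follow-up visit score to lose.
- Removed unless all four are attended: 1 − 0.9⁴ = 34.4%. Patients who attended month 1 and are then removed make up 0.9 × (1 − 0.9³) = 24.4% of all patients. That is 24.4 / 34.4 = 71% of those removed, and 1 − 0.9³ = 27% of those with a 1-month score.

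The wording of section 8(1) favours the first reading. So does the reason given in criterion 6, that data are hard to collect. The planned mixed model, which can use patients with some visits missing, fits it too. Nothing states that the second reading is excluded.

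**The case against.** Collecting questionnaires at clinic visits is a common choice, and both arms have the same visits with tests of their own, inside a wide window. The arm-specific incentive may therefore be weak. The pilot gives no support for loss through missed visits: its six drop-outs were four for final stage and two refusals, and it had no control arm. A 15- or 20-point deficit is 1.5 or 2 SDs on the plan's own SD. With the 10% versus 5% split and a deficit of 5 to 10 points, the shift is only 0.25 to 0.5 points against a standard error of 1.75. The elimination rule, read naturally, touches almost nobody. How missing data are analysed may also be settled in a statistical analysis plan that is not shown.

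Most of this stands, and it limits the point to a possibility of unknown size. It does not remove it. How the questionnaire is collected and who is eliminated are conduct rules fixed in the protocol, and no later analysis plan can recover a questionnaire that was never offered. The two readings of criterion 6 also remain open.

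A reader might infer that months 6 and 12 are the most exposed. The documents do not support that: neither arm has a programme visit then, so the arm-specific incentive is absent and only ordinary attrition remains. A reader might also infer that the contacts exclude the questionnaire. Section 8(1) is silent on this; it does not forbid it.

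**Conclusion.** The point holds as a design weakness that could bias the primary comparison, not as a demonstrated bias. The self-reported score is tied to visits with no stated alternative, and at both candidate primary time points only the control programme is delivered at the visit. On assumed missingness of 10% versus 5% and a deficit of 5 to 20 points, the shift is 0.25 to 1.0 points towards the app, 5% to 20% of the planned difference. It is zero if missingness and deficits are equal across arms. Larger gaps between the arms would give more, but no rate of missed visits is available to say which case applies.

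A reader might conclude that about a third of patients, or most of those with a 1-month score, would be eliminated. The first needs the less natural reading of criterion 6 and an assumed 10% miss rate per visit; the second is false even then, since the figure is 27%. What can be said is that criterion 6 is ambiguous, and that one of its readings would discard scores already obtained. This is a cheap improvement.

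**What to change.** 1. In section 8(1), state that a patient who misses a visit but is reached through the phone or text contacts already scheduled is offered QLQ-C30 and STO22 by phone or link within the visit window, and that the mode of completion is recorded. State also that these contacts start early enough to fall inside the window.
2. In criterion 6 (synopsis and section 4(4)) and in the last sentence of section 8(1), replace the attendance-based elimination with: *Missing one or more visits is not a reason for removal; all questionnaires obtained are kept and analysed in the randomised arm.* Confine this to missed visits. The other drop-out criteria, including withdrawal at the patient's request, are left to separate review; a broader rule would collide with criteria 1 to 4.

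The cost is a short amendment and some coordinator time during contacts that are already planned. The downside is small: a few scores will come by a different mode, which can be checked in a sensitivity analysis.
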